## Abstract

**Background:**

Saphenous vein graft disease remains a major limitation of coronary artery bypass graft surgery. The process of saphenous vein intimal hyperplasia begins just days after surgical revascularization, setting the stage for graft atherosclerotic disease and its sequalae. Clopidogrel improves outcomes in patients with atherosclerotic disease, and is effective at reducing intimal hyperplasia in animal models of thrombosis. Therefore, the goal of this study will be to evaluate the efficacy of clopidogrel and aspirin therapy versus aspirin alone in the prevention of saphenous vein graft intimal hyperplasia following coronary artery bypass surgery.

**Methods:**

Patients undergoing multi-vessel coronary artery bypass grafting and in whom at least two saphenous vein grafts will be used are eligible for the study. Patients will be randomized to receive daily clopidogrel 75 mg or placebo, in addition to daily aspirin 162 mg, for a one year duration starting on the day of surgery (as soon as postoperative bleeding has been excluded). At the end of one year, all patients will undergo coronary angiography and intravascular ultrasound assessment of one saphenous vein graft as selected by randomization. The trial will be powered to test the hypothesis that clopidogrel and aspirin will reduce vein graft intimal hyperplasia by 20% compared to aspirin alone at one year following bypass surgery.

**Discussion:**

This trial is the first prospective human study that will address the question of whether clopidogrel therapy improves outcomes and reduces saphenous vein graft intimal hyperplasia following cardiac surgery. Should the combination of clopidogrel and aspirin reduce the process of vein graft intimal hyperplasia, the results of this study will help redefine modern antiplatelet management of coronary artery bypass patients.

Despite its established benefit in patients with coronary artery disease, aspirin therapy has numerous limitations. It is a relatively weak antiplatelet agent and has no effect on thrombin, which is believed to play a major role in acute coronary syndrome [26]. Even with aspirin therapy for secondary prevention, a large number of recurrent events occur [27]. A significant proportion of patients undergoing CABG may be aspirin resistant, defined as undetectable platelet inhibition after one week of therapy [28,29]. Depending on the population studied and the specific definition of aspirin resistance, anywhere from 10–40% of patients appear to have an inadequate antiplatelet response to aspirin [28,30]. Such patients appear to be at increased risk for the development of vascular events. In theory, these aspirin-resistant patients may derive particular benefit from additional antiplatelet therapy [31].

Clopidogrel is a thienopyridine antiplatelet agent that inhibits ADP-dependent platelet activation and aggregation [32]. Sevenfold more potent than ticlopidine, clopidogrel is free of its adverse side effects such as neutropenia, diarrhea and rash [33]. Unlike aspirin [24,34], clopidogrel has been shown to inhibit the process of platelet-mediated intimal proliferation and smooth muscle hyperplasia in laboratory experiments. In a cell culture model, clopidogrel significantly inhibited platelet adhesion to immobilized fibrinogen and also inhibited platelet-dependent mitogenic signaling and DNA synthesis in cultured coronary artery smooth muscle cells [35]. Similarly, in animal thrombosis models, clopidogrel but not aspirin significantly inhibited platelet-mediated intimal proliferation and smooth muscle hyperplasia [33,36]. Furthermore, the combination of clopidogrel with aspirin led to potent synergistic antithrombotic effects and a decrease in myointimal proliferation compared to either therapy alone [24,36,37].

Several large clinical trials have demonstrated that clopidogrel reduces ischemic events and mortality in patients with coronary and vascular disease [38-41]. In the CAPRIE (Clopidogrel versus Aspirin in Patients with Ischemic Events) trial, clopidogrel (75 mg/day) was demonstrated to be significantly more effective than aspirin (325 mg/day) in preventing vascular thrombotic events (ischemic stroke, MI or vascular death) in patients with clinical evidence of atherosclerotic disease (clopidogrel 9.78% vs. aspirin 10.64%, relative risk reduction [RRR] 8.7%, p = 0.045) [38]. In patients presenting with acute coronary syndromes, the CURE (Clopidogrel in Unstable angina to prevent Recurrent ischemic Events) study demonstrated that the combination of clopidogrel and aspirin was more effective at reducing the primary outcome (cardiovascular death, nonfatal MI or stroke) compared to aspirin alone (clopidogrel and aspirin 9.3% vs. aspirin alone 11.4%, RRR 20%, p < 0.001) [40]. Subgroup analysis from these trials suggested that patients that underwent surgical revascularization also benefited from clopidogrel [39,42,43]. However, no trial to date has prospectively evaluated the combined effects of clopidogrel plus aspirin on saphenous vein graft disease after CABG.

There currently exists a clinical equipoise regarding the optimal antiplatelet therapy for patients who have undergone coronary artery bypass surgery. While some clinicians believe in the beneficial effects of clopidogrel, the increased risk of bleeding and the lack of data in CABG patients make it impossible to establish definitive recommendations. We therefore propose the Clopidogrel after Surgery for Coronary Artery Disease (CASCADE) study, a randomized, placebo-controlled trial comparing clopidogrel plus aspirin versus aspirin alone in CABG patients revascularized with saphenous vein. The primary aim of this study will be to evaluate the effect of combined antiplatelet therapy on the reduction of SVG intimal hyperplasia one year after CABG, through the assessment of intimal area by intravascular ultrasound (IVUS). Secondary aims will evaluate the safety of clopidogrel administration following CABG with regards to bleeding complications. We hypothesize that the combination of clopidogrel with aspirin will reduce the SVG intimal hyperplasia (intimal area) by 20% one year post-CABG compared to the usual antiplatelet therapy of aspirin alone.

## Methods

### Study Population and Recruitment Procedure

The study population will include all patients undergoing multi-vessel elective or urgent CABG using at least two saphenous vein grafts at the University of Ottawa Heart Institute (OHI) over the study period (see Table 1 for inclusion and exclusion criteria). Patients undergoing off-pump CABG (OPCAB) will also be eligible for this study, as long as at least two saphenous vein grafts are used. OPCAB is performed in order to avoid the hazards associated with standard CABG, such as cardiopulmonary bypass and aortic cross-clamping, and is carried out at the discretion of the surgeon in patients deemed to be at higher risk of thromboembolic or renal complications during surgery. All CABG patients at the OHI will be triaged pre-operatively, and study eligible patients will be selected and approached by the study nurse to explain the trial and obtain consent.

### Description of Intervention and Control

A prospective randomized double-blinded placebo-controlled study will be conducted from November 2005 to November 2007 in order to achieve the study objectives. Patients will be recruited over the first 12 months of the study, and graft evaluation for each patient will occur over the following 12 months (one year after surgery for each patient). Patients will be randomized into an experimental group (receiving clopidogrel) or a control group (placebo). The placebo and clopidogrel medications will be prepared by the Bristol Myers-squibb Sanofi Canada Partnership and appear identical. Medication administration and data collection will be performed in a double-blind manner, such that neither the patient nor the healthcare personnel will be aware of the medication assignment. Recruitment and written consent will be performed prior to surgery. However, patients will not be randomized until after surgery has been completed and clinical stability ensured. Patients that are bleeding excessively after surgery (chest tube output > 200 cc/hr) or those requiring high levels of hemodynamic support (more than 2 inotropes and/or intra-aortic balloon pump) will not be randomized into the study.

After surgery, the study medication will be administered via nasogastric tube when the chest tube drainage has decreased to ≤50 cc/hr for 2 hours. Each patient will receive either clopidogrel 75 mg or placebo, in addition to enteric coated aspirin 162 mg (Figure 1). The study drug and aspirin 162 mg will be repeated orally in the same dose once daily for the duration of one year. Because post-CABG patients are relatively aspirin resistant following surgery, the aspirin dose of 162 mg will ensure adequate platelet inhibition in those patients randomized to aspirin alone. Furthermore, 162 mg falls within the safety window of combining aspirin with clopidogrel [30,40,44].

**Figure 1 F1:**
[figure not shown]
text

### Allocation Procedure

A stratified random design allocation will be utilized to account for the presence or absence of diabetes, as well as the use or nonuse of cardiopulmonary bypass (standard CABG versus OPCAB). A block randomization technique will ensure an equal distribution of diabetic patients in both arms of the trial and an equal distribution of OPCAB patients. The randomization schedule will be generated using SAS 9.1 software (SAS, Cary, NC). All patients and study personnel will be blinded to the treatment assignment, which will be performed by the hospital pharmacy.

### Concomitant Medication and Treatments

Patients will receive concomitant therapies in both groups as recommended by the current American College of Cardiology / American Heart Association guidelines. This will include smoking cessation counseling and the administration of aspirin, beta blockers, angiotensin converting enzyme inhibitors, and lipid lowering medications. Target LDL values will be those recommended as per current guidelines [45-47] and will be assessed during the study follow-up period. Routine peptic ulcer prophylaxis will not be administered in order to fully evaluate gastrointestinal side effects.

Diabetic patients will be eligible for enrollment in this study, regardless of their preoperative need for insulin therapy, and will be allocated equally into both groups through stratified randomization. Diabetic patients will have aggressive perioperative glycemic control, including an intravenous insulin infusion both in the operating room and in the intensive care unit, and a subcutaneous insulin sliding scale while recovering on the surgical ward. Once drinking well, diabetic patients will be restarted on their original preoperative diabetic regimens (oral agents and/or insulin therapy). The treatment of diabetes during this study will be closely monitored in collaboration with an endocrinologist specializing in the management of diabetes.

### Primary Outcomes

The primary endpoint of this study will be to assess whether the addition of clopidogrel to aspirin reduces intimal hyperplasia in saphenous vein grafts 12 months after bypass surgery, as assessed by IVUS. Patients will undergo IVUS imaging 12 months post-CABG, and the average intimal area in the proximal 40 mm of one vein graft per patient will be assessed.

### Secondary Outcomes

At the time of intravascular ultrasound, coronary and graft angiography will also be performed to assess vein graft patency and areas of stenosis. Although this trial will not be sufficiently powered for such a purpose, this data will be obtained whilst gathering information pertaining to the primary outcome.

Endpoints related to safety will also be documented, both at the time of surgery as well as during the one year of study drug administration. After surgery, data will be recorded regarding chest tube blood loss, blood product transfusions, bleeding requiring tube thoracostomy or sternal re-opening, perioperative MI, and gastrointestinal complications. Complete blood counts (CBC) will assess the hemoglobin level in the immediate postoperative period and during the one year follow-up. In addition, the incidence of major adverse cardiovascular events following CABG (mortality, MI, cerebrovascular accident, hospitalization for coronary ischemia, need for coronary intervention) will be recorded.

### IVUS Procedure

Intravascular ultrasound will be used to assess the area of intimal hyperplasia present in saphenous vein grafts at 12 months after surgery. IVUS differs from angiography by providing cross-sectional images of both the vessel wall and lumen with high resolution. The process of intimal hyperplasia is easily detectable and quantifiable by IVUS, but may completely escape visualization by angiography. At one year following CABG, vein graft intimal hyperplasia is universally present.

Efforts will be made to schedule all patients at 52 ± 2 weeks from the day of randomization (Figure 1). The IVUS procedure will first start with angiography of the native coronary arteries and the coronary bypass grafts. This will allow assessment of the progression of native coronary artery atherosclerosis (both in grafted and non-grafted vessels). Patency of all bypass grafts will be scored using 1) the Fitzgibbon method [14] and 2) the TIMI classification [48]. Patency of the coronary arteries will be assessed by the TIMI method.

IVUS studies will be performed using a 40 MHz imaging catheter (Atlantis^® ^SR Pro, Boston Scientific). This catheter is a monorail system and has 6F guiding catheter compatibility. All IVUS imaging will be done with the administration of unfractionated heparin (70 units per kg, minimum 4000 units) before the introduction of the guidewire into a vein graft. Each patient will have at least two vein grafts implanted at the time of surgery. However, imaging of more than one graft is not clinically advisable for safety and practical reasons. In order to minimize bias, the cardiologist performing the IVUS procedure will be blinded to the treatment allocation, and the selection of the SVG for IVUS imaging will be randomized. For this purpose, a sequence randomization scheme (based on the number of vein grafts) will produce a random sequence of numbers for each patient, such as "2, 1 and 3". These numbers will correspond to the position of the proximal anastomosis of each SVG on the ascending aorta (by increasing number from cranial to caudal, starting from 1). The graft whose random number is produced first will be selected for intubation with the IVUS catheter, unless 1) this particular graft showed more than 50% stenosis on the selective angiography performed immediately prior, or 2) access to this graft is technically difficult (graft tortuosity, difficult graft intubation). If any of the above two instances is encountered, the graft with the next number in the randomization sequence will instead be selected for IVUS, and so on. Graft exclusion for whatever basis (either because >50% stenosis or technically difficult access) will be recorded for all patients in each group.

Once the randomized graft selection has been completed, the actual IVUS procedure will take place. Intracoronary nitroglycerin (200 μg) will be given before advancing the IVUS catheter, and a 6F guiding catheter will be used to engage the vein graft. Then, a 0.014" coronary angioplasty guidewire will be advanced distally through the vein graft and positioned into the native coronary artery. The IVUS catheter will then be advanced into the graft at least 50 mm beyond the aorto-ostial anastomosis. The guiding catheter will then be disengaged to ensure visualization of the aorto-ostial anastomosis on pullback. This is essential because the aorto-ostial anastomosis will be the only landmark available to assure measurements of the proximal portion of each graft are comparable between groups. IVUS imaging will be done using a validated motorized pullback device at 0.5 mm/sec. Each study will be recorded on a separate S-VHS videotape. Only one quality pullback will be needed per graft, but a second pullback may be repeated if the first set of pullback images were judged suboptimal in quality.

### IVUS Analysis

The IVUS images will be sent to an independent core laboratory and interpreted by an experienced cardiologist blinded to treatment allocation. The methods for the analysis have been previously reported and validated [49]. Briefly, using the aorto-ostial anastomosis as a landmark, the most proximal 40 mm of vein graft will be analyzed. The video images will be digitized and measurements of lumen, intimal hyperplasia, and external elastic lamina areas will be available for each digitized cross section. Intimal hyperplasia volumes will be computed by multiplying the corresponding areas of each of the cross-sections by the distance between slices and by adding the products. For the purpose of this study, the mean plaque area per patient for the 40 mm-analyzed segment will be used for comparison between treatment groups.

### Sample Size

The trial will be powered to test the hypothesis that clopidogrel and aspirin should reduce vein graft intimal hyperplasia by 20% compared to aspirin alone at one year following bypass surgery. According to Hozumi et al., at one year, the mean intimal area of angiographically normal saphenous vein grafts is 5.26 mm^2^, with a standard deviation of 1.38 mm^2 ^[50]. Intravascular ultrasound imaging will be performed at follow-up in one vein graft per patient. In order to account for potential angiographic refusals and study withdrawals, approximately 100 patients in total will be required to test the null hypothesis with an α value of 0.05 and a power of 0.90.

### Data Collection and Safety Monitoring

Intimal area will be recorded at the time of IVUS one year after CABG. Vein graft patency and stenosis will be assessed by angiography. The incidence of major adverse coronary events and bleeding complications will be documented during postoperative clinic visits at one month, six months and twelve months after surgery. Telephone home assessments every three months will also be used to document events. All serious adverse events will be reported to the ethics committee. The development of serious adverse events that might be attributable to clopidogrel will lead to the termination of the study drug.

### Ethics

The study will adhere to the highest research ethics standards of the OHI. This protocol follows the CONSORT guidelines [51] and was approved on July 19, 2005 by the University of Ottawa Heart Institute Human Research Ethics Board.

### Statistical Analysis

Vein graft intimal area, the primary outcome of the study, will be compared between the two randomization groups using two-sided Student's t tests. Vein graft patency will be compared using a Fisher's exact test. With respect to the secondary outcomes, continuous data will be compared between the two groups using two-sided Student's t tests, two-sample Wilcoxon rank-sum tests, or ANOVA as appropriate, and a Fisher's exact test will be used for categorical data. In order to assess possible interactions between patient characteristics (such as diabetes) and treatment outcomes, an exploratory analysis using multivariate linear regression will be performed. In the improbable event that all vein grafts are occluded and IVUS cannot be performed in a particular patient undergoing the one-year study, a value of five times the mean intimal area (decided *a priori*) will be assigned for that patient.

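### Randomisation is stratified by diabetes and bypass use, but the primary t test ignores both; if they predict intimal area, the test is mildly conservative and gives up a little precision

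*Protocol article*

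**What the plan says.** The Allocation Procedure section of the protocol article says "A stratified random design allocation will be utilized to account for the presence or absence of diabetes", and names the use or nonuse of cardiopulmonary bypass as a second factor. Blocks are used so that both factors are evenly spread over the arms.

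The Statistical Analysis section fixes the primary test: "Vein graft intimal area, the primary outcome of the study, will be compared between the two randomization groups using two-sided" Student's t tests. No stratum term enters that comparison. The same section plans one multivariable regression, labels it exploratory, and directs it at interactions between patient characteristics (diabetes is the example) and treatment. It does not adjust the primary comparison.

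The Sample Size section requires "approximately 100 patients in total will be required" to "test the null hypothesis with an α value of 0.05 and a power of 0.90".

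**The concern.** Blocking within strata removes most of the between-stratum variation from the difference in arm means. A two-sample t test does not use this: its pooled variance still counts that variation as error. If the strata are prognostic, the reported standard error exceeds the true one, the 95% confidence interval covers more than 95% of the time, and the test rejects a true null hypothesis less than 5% of the time.

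At stake is some precision in the main result of a small trial. The article names a specific primary test, so the point concerns a stated rule that does not match the stated design. It is not about detail left to an analysis plan that is not shown.

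**Working it through.** **Inputs from the article (Sample Size and Statistical Analysis sections).** The mean is stated as "the mean intimal area of angiographically normal saphenous vein grafts is 5.26" mm², "with a standard deviation of 1.38" mm². The target effect is a 20% reduction, and the test is two-sided at α = 0.05 with power 0.90.

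**Inputs assumed.** 1:1 allocation, and R², the share of outcome variance explained by the two strata, from 0 to 0.15. The article gives no value for R². The simulations also assume 30% diabetic patients, 15% off-pump patients and blocks of 4.

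**Step 1: the plan's own figure.**
- Difference: 0.20 × 5.26 = 1.052 mm². Standardised: 1.052 / 1.38 = 0.762.
- Normal approximation: n per arm = 2 × (1.960 + 1.282)² × 1.38² / 1.052² = 36.2, so 37. The exact t calculation needs 38 per arm, or 76 in total.
- 76 / 0.76 = 100. The stated total therefore fits a loss of about 24%, but the article gives no loss rate, so 100 is consistent with the inputs rather than strictly reproducible. I use 76 analysed patients below.
- This calculation uses the full SD and an unadjusted test.

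**Step 2: effect of ignoring the strata, with perfect balance among analysed patients.** The t test reports a standard error of about 1.38 × √(2/38) = 0.317. The true one is 0.317 × √(1 − R²). Let δ = 0.762 × √19 = 3.32.
- Actual type I error = 2 × [1 − Φ(1.96 / √(1 − R²))]
- Power, t test = Φ((δ − 1.96) / √(1 − R²))
- Power, adjusted = Φ(δ / √(1 − R²) − 1.96)

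| R² (assumed) | True SE / reported SE | Type I error, t test | Power, t test | Power, adjusted |
|---|---|---|---|---|
| 0 | 1.000 | 5.0% | 0.914 | 0.914 |
| 0.05 | 0.975 | 4.4% | 0.919 | 0.926 |
| 0.10 | 0.949 | 3.9% | 0.925 | 0.939 |
| 0.15 | 0.922 | 3.4% | 0.930 | 0.950 |

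**Step 3: loss after randomisation.** If a random 76 of 100 patients are analysed, about 0.76 × R² of the variance is removed by the blocking instead of R². Replacing R² by 0.76 × R² in the two t test formulas gives, for R² = 0.05, 0.10 and 0.15:
- type I error 4.6%, 4.1% and 3.7%;
- t test power 0.918, 0.922 and 0.926, against the adjusted values in the table. The gain is then at most 0.950 − 0.926, or 2.4 points.

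**Step 4: simulation.**
- Complete follow-up, 38 per arm: at R² = 0.05 and 0.10 the reported standard error is too large by about 2% and 4%. Type I error is 4.5% and 3.8%. Power is 0.910 against 0.918, and 0.917 against 0.934. At R² = 0 both analyses give 0.907.
- 100 randomised, 76 analysed, random loss: at R² = 0.05, 0.10 and 0.15, type I error is about 4.5%, 4.4% and 3.7%. Power is 0.91, 0.92 and 0.92 for the t test against 0.92, 0.93 and 0.95 adjusted.

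**Step 5: the value for total occlusion.** The Statistical Analysis section assigns five times the mean intimal area when every vein graft is occluded. Taking the planning mean, that is 5 × 5.26 = 26.3 mm². With R² = 0.10, 76 of 100 analysed, and occlusion assumed unrelated to arm or strata, simulated power is 0.613 for the t test against 0.624 adjusted if 1% are occluded, and 0.302 against 0.304 if 3% are. The gain from adjustment shrinks to about one point or less. The fall in power itself comes from the assigned value, which is a separate matter.

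**The case against.** The strongest reply is that little is lost. Every t test power in Steps 2 to 4 is above the planned 0.90, because the sample size was set for an unadjusted test with the full SD. The error is in the safe direction. The loss exists only if the strata are prognostic, which the article never quantifies; at R² = 0 adjustment changes nothing. All of this stands, and it sets the size of the point.

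Two stronger readings are tempting and should be resisted.
- A reader might infer that the standard error is certainly too large and precision certainly lost. The article supports only the conditional statement. The choice of stratification factors suggests that the investigators thought they might matter, but gives no R².
- A reader might infer that stratifying was wasted. The stated aim in the Allocation Procedure section is even distribution of diabetic and off-pump patients, and blocking delivers that whatever test follows. The unadjusted estimate keeps the benefit too: in the complete follow-up simulation its true standard deviation falls to 0.304 at R² = 0.10 while the reported standard error stays near 0.316. Only the reported precision misses it.

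It can also be said that covariate adjustment is often left to an analysis plan. That softens the point but does not remove it, since the article already names the primary test.

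**Conclusion.** The mismatch between a stratified, blocked allocation and an unadjusted primary t test is in the text. Its consequence is conditional and modest: a somewhat overstated standard error and a mildly conservative test if diabetes and bypass use predict intimal area. The estimate is not biased, type I error is not inflated, and this choice does not endanger the planned power. For assumed R² from 0 to 0.15, type I error falls from about 5% to about 3.4–3.9% at the upper end, and adjustment is worth about 0 to 3 points of power, less once any patient is assigned five times the mean. These sizes rest on the assumed R², 1:1 allocation, 76 analysed patients and loss unrelated to arm or outcome. This is a low-cost improvement in efficiency and in the accuracy of the confidence interval, not a flaw that puts the trial's conclusion at risk.

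**What to change.** In the Statistical Analysis section, make the primary analysis a linear model of mean intimal area on treatment, with diabetes and use of cardiopulmonary bypass as main-effect covariates. Report the adjusted difference with its 95% confidence interval, and keep the unadjusted two-sided t test as a sensitivity analysis. The exploratory interaction regression can stay as it is.

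The cost is one sentence and two degrees of freedom (72 instead of 74 with 76 patients). Both factors are needed for the stratified allocation, and because randomisation follows surgery, bypass use is known by then. No new data are needed and the sample size does not change. Making the change before unblinding also avoids a later choice between the t test and a regression.

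### The only tests named for continuous safety data such as hemoglobin are unadjusted, which costs precision but causes no bias; transfusion after the first dose can separately shrink an early difference

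*Protocol article*

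**What the plan says.** Secondary Outcomes lists hemoglobin as a repeated safety measure: "Complete blood counts (CBC) will assess the hemoglobin level in the immediate postoperative period and during the one year follow-up". The same section lists other bleeding measures beside it: "data will be recorded regarding chest tube blood loss, blood product transfusions, bleeding requiring tube thoracostomy or sternal re-opening".

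Statistical Analysis covers all continuous secondary outcomes in one sentence: "continuous data will be compared between the two groups using two-sided Student's t tests, two-sample Wilcoxon rank-sum tests, or ANOVA as appropriate". For the others, "a Fisher's exact test will be used for categorical data". The only regression in the section, "an exploratory analysis using multivariate linear regression will be performed", serves to look for interactions between patient characteristics and treatment, not to adjust hemoglobin for an earlier value. Hemoglobin is not mentioned by name in that section.

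Description of Intervention and Control fixes the timing. On randomization: "patients will not be randomized until after surgery has been completed and clinical stability ensured". On the first dose: "the study medication will be administered via nasogastric tube when the chest tube drainage has decreased to ≤50 cc/hr for 2 hours".

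**The concern.** Bleeding safety is the stated secondary aim (Background), and the Discussion says the trial will answer whether adding clopidogrel is safe. With about 100 patients in total, bleeding events will probably be few, so the continuous bleeding measures carry a good part of the sensitivity.

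Two separate matters arise for hemoglobin.

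1. **Precision.** Much of the spread between patients comes from blood lost in surgery, before randomization and before any study drug. A t test, rank-sum test or one-way ANOVA leaves that spread in the error term. A pre-dose count used as covariate would remove part of it.
2. **Masking.** Transfusion after the first dose raises hemoglobin in the patients who bled. If one arm bleeds more and is transfused more, the early arm means move together. The plan does not say how such transfusions enter the hemoglobin comparison.

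At stake is the sensitivity of one supportive safety measure. The masking, where it occurs, works toward showing no difference.

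**Working it through.** **Inputs.** The documents give about 100 patients in total (Sample Size) and two-sided tests (Statistical Analysis). They state no mean, SD, correlation, power or transfusion rule for hemoglobin, so the plan has no hemoglobin figure to reproduce. Every hemoglobin input below is an assumption, and the transfusion triggers are devices of the calculation, not proposals.

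**Step 1: precision.** With correlation ρ between the pre-dose and later value, the standard error (SE) after covariate adjustment is √(1 − ρ²) times the unadjusted one. The equivalent gain in patients is 1/(1 − ρ²). For power, assume SD 1.3 g/dL, 45 evaluable patients per arm and a difference of 0.7 g/dL:

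- unadjusted SE = 1.3 × √(2/45) = 0.274 g/dL
- 0.7/0.274 = 2.55
- two-sided power at 0.05 (noncentral t) = 0.714

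| ρ | SE factor | SE cut | Patient equivalent | Power |
|---|---|---|---|---|
| unadjusted | 1 | none | 1 | 0.714 |
| 0.3 | √0.91 = 0.954 | 5% | 1/0.91 = 1.10 | 0.754 |
| 0.5 | √0.75 = 0.866 | 13% | 1/0.75 = 1.33 | 0.831 |
| 0.7 | √0.51 = 0.714 | 29% | 1/0.51 = 1.96 | 0.943 |

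A simple change score is not a safe substitute. Its SE factor is √(2(1 − ρ)): 1.18 at ρ = 0.3 (worse than no adjustment), 1.00 at 0.5 and 0.77 at 0.7.

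**Step 2: does leaving out the pre-dose value bias the result?** No. Randomization balances it in expectation. In a simulation with no true effect and 50 per arm, the raw t test rejected in 4.2% to 5.6% of trials, close to the nominal 5%.

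**Step 3: masking by transfusion after the first dose.** Assume 50 per arm, control mean 9.5 g/dL, SD 1.3, a true fall of 0.8 g/dL on study drug, and 1 g/dL gained per unit, with units given until the trigger is reached. Results from 4000 simulated trials per trigger:

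| Assumed trigger (g/dL) | Observed difference (g/dL) | t-test power | Rank-sum power, transfused ranked lowest by units | Fisher power, proportion transfused |
|---|---|---|---|---|
| 7.5 | 0.65 | 0.83 | 0.85 | 0.31 |
| 8.0 | 0.55 | 0.79 | 0.84 | 0.47 |
| 8.5 | 0.43 | 0.73 | 0.85 | 0.58 |
| 9.0 | 0.30 | 0.61 | 0.84 | 0.63 |

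**Step 4: does the pre-dose covariate cure the masking?** No. In a second simulation (SD 12 g/L, true fall 6 g/L, triggers 80 or 90 g/L, rise 10 or 20 g/L after transfusion), the raw difference shrank to 2.1 to 4.8 g/L, and adjustment for the pre-dose value gave the same 2.1 to 4.8 g/L. Entering post-dose transfusion as a covariate gave 2.3 to 4.1 g/L, still short of 6. It is also unsound in principle, because transfusion is a consequence of the bleeding being measured. In these settings the proportion transfused differed between arms by 12 to 20 percentage points, and Fisher's exact test detected that in 24% to 47% of trials.

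**The case against.** The strongest reply is that the article gives a generic menu of tests for all continuous secondary data, and that covariates and transfusion handling for one supportive laboratory measure are commonly left to an analysis plan that is not shown. That lowers the severity. It does not remove the point, because the article does fix the class of test, and that class is less precise than adjusting for a correlated pre-dose value.

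Several further objections stand:

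- A reader might infer that a raw level is certain to be compared. The outcome is described as a hemoglobin level, but no sentence rules out change from an earlier count.
- A reader might infer that a pre-dose count is already in the data. The documents time the first dose but do not say when the immediate postoperative count is drawn relative to it.
- A reader might infer that the unadjusted tests are themselves biased toward no difference. They are not: omitting the pre-dose value costs precision only. Transfusion attenuates the difference only relative to what it would have been without transfusion, a target the documents do not state.
- A reader might infer that the whole bleeding signal is lost. It is not: transfusions, chest tube loss and re-opening are recorded separately, and transfusion does not restore chest tube loss. Masked hemoglobin would tend to show as more transfusion, though the power to see that is modest.
- A comparison that ranks transfused patients lowest is debatable as a main analysis. Blood products are recorded without red cells being singled out, and a patient transfused after the first dose for blood lost before it would count as a poor outcome.

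**Conclusion.** The point holds in limited form. The only tests named for continuous secondary data, hemoglobin among them, are unadjusted. The loss is one of precision: 5%, 13% or 29% of the standard error at assumed correlations of 0.3, 0.5 or 0.7. Nothing in the documents says which correlation applies, and 0.7 is optimistic for counts taken months later.

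Attenuation by transfusion is a separate matter that mainly concerns early counts. Under the assumptions shown, a true 0.8 g/dL appears as 0.65 to 0.30 g/dL. At the two lower triggers the gap in power between the t test and the ranked comparison is small (0.83 against 0.85, and 0.79 against 0.84); it is large only at the highest (0.61 against 0.84).

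Severity is low. The intimal-area analysis and the sample size are unaffected.

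**What to change.** In Statistical Analysis, add for hemoglobin: counts after the first dose will be analysed by ANCOVA, or by a mixed model for repeated measures with treatment, visit and their interaction, with the last hemoglobin before the first dose as covariate where such a count is available. Each count will be labelled as before or after the first dose.

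As a supplementary analysis of the early counts only: compare the arms by a rank-sum test that places patients given red cells after the first dose below all others. Report it next to the observed means and the comparison of transfusions. Do not adjust for post-dose transfusion as a covariate.

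The cost is modest but goes beyond wording. Counts and transfusions must be timed against the first dose, red cells must be separated from other blood products, and the adjustment depends on a pre-dose count existing. The adjusted model recovers precision only; it does not undo the masking, which is why the supplementary comparison is needed.
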